#### Training

Several information sessions will be organized for the members of the palliative care team on specific early cancer treatments and their possible side effects. The senior oncologists of each department will give a presentation with the focus on cancer etiology, cancer treatment (chemotherapy, radiotherapy, etc.), specific symptoms and side effects and an additional information session will be organized by the researchers on the implementation of the intervention, with topics such as the use and interpretation of the ESAS, the use of the interview form and the referral checklist.

#### Standard care

In addition to medical treatment, all patients with advanced cancer treated in the Ghent University Hospital receive extensive standard paramedical care. (1) A clinical oncology nurse specialist supports the patients throughout their disease trajectory by providing information on treatment and possible side effects and coordinates hospital appointments. This nurse is available during hospital visits and can be telephoned during working hours. (2) An oncology psychologist helps patients and informal caregivers to cope with the psychosocial implications of cancer and cancer treatment and provides further consultations for the patient and/or their family members at the request of the patient. (3) A dietician has a standard introductory consultation with cancer patients diagnosed with oesophageal cancer, stomach cancer, pancreatic cancer and head and neck cancers. All other cancer patients are screened for weight loss during their hospital stay or treatment and whenever significant weight loss is found, the dietician is consulted. (4) The social worker helps and supports patients and their relatives in dealing with the consequences of the disease and treatment in their everyday life. They make practical arrangements related to the organization of specific assistance at home and they provide information about financing, social security, insurance and transitions to residential care. The social worker attends at the request of the patient, the oncologist or the oncology nurse. (5) In routine clinical practice in the Ghent University Hospital, the members of the palliative care team are not structurally involved in the treatment trajectory of the cancer patient but at the request of the patient or at the discretion of the attending physicians, or a member of the paramedical team in cases of difficult symptom control and issues related to end-of-life care, such as advance directives. This referral mostly occurs late in the treatment trajectory.

### Outcome measures

#### Study objectives

The primary objective of this study is to assess the impact of this intervention’s systematic early integration of palliative care on the patient’s quality of life. The secondary objectives are (1) to assess the impact on the patient’s median survival time, mood and illness understanding, (2) the impact on informal caregivers’ quality of life, mood, illness understanding and satisfaction with care during treatment and after the death of the patient and (3) to examine whether systematic early integration of palliative care, alongside hospital treatment and treatment characteristics, influences advance care planning and end-of-life decision-making.

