##### Patient and informal caregiver questionnaires

Quality of life of the patient will be measured with the use of the European Organisation for Research and Treatment of Cancer Quality of Life Questionnaire (EORTC QLQ C30) and the McGill Quality of Life Questionnaire (MQOL) [17–19]. The MQOL has been selected because it addresses the existential aspects of quality of life as well as the physical, emotional and social aspects of quality of life. A recent review qualified both its content and construct validity as high [20]. The mood of the patient will be measured by two instruments: the Hospital Anxiety and Depression Scale (HADS) and the Patient Health Questionnaire 9 (PHQ-9) [21–24]. Illness-understanding will be measured by a forward-backward translation of the questionnaire developed by the researchers of the previously mentioned study of palliative care for patients with metastatic non-small-cell lung cancer [4]. Data on mood, quality of life, illness understanding and satisfaction with care of the informal caregivers will be obtained by self-assessment instruments: HADS, PHQ-9, the Short Form-36 Health Survey (SF-36) a questionnaire for illness understanding and by the FAMCARE respectively [25]. A forward-backward translated and tested version of the FAMCARE will evaluate the satisfaction with care of the informal caregivers [26].

The surveys filled out by patients and informal caregivers, their frequency and the timing of completion are detailed in Table 3. The patient will complete the baseline questionnaires before randomization and the follow-up questionnaires with regard to quality of life, mood and illness-understanding firstly after 12 weeks and thereafter every six weeks. Change from baseline to 12 weeks after inclusion is chosen because approximately 80 % of patients are expected to be alive at 12 weeks after inclusion [4]. The informal caregivers will complete the baseline questionnaire before randomization and the follow-up questionnaires firstly after 12 weeks and then every six weeks. If the patient dies the informal caregiver is asked to fill out the questionnaire once more 12 weeks after the death.

**Table 3 Tab3:** Types of patient and informal caregiver questionnaires and frequency and timing of completion

	Week					
	Baseline	12	18	24	…	12 weeks after patient’s death
PATIENT FORMS						
EORTC QLQ C30 and MQOL	X	X	X	X	X	
PHQ-9 and HADS	X	X	X	X	X	
Illness-understanding Questionnaire	X	X	X	X	X	
INFORMAL CAREGIVERS FORMS						

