General Health SF-36	X	X	X	X	X	X
PHQ-9 and HADS	X	X	X	X	X	X
FAMCARE	X	X	X	X	X	
Illness-understanding Questionnaire	X	X	X	X	X	

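### Caregiver satisfaction after the patient's death is part of secondary objective 2, but Table 3 does not schedule FAMCARE after death

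*Protocol article*

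**What the plan says.** Under Study objectives, the second secondary objective lists four caregiver outcomes: quality of life, mood, illness understanding and satisfaction. It ends with the words "satisfaction with care during treatment and after the death of the patient".

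Under Patient and informal caregiver questionnaires, one instrument is assigned to satisfaction: "A forward-backward translated and tested version of the FAMCARE will evaluate the satisfaction with care of the informal caregivers". The same section hands timing to the table: "The surveys filled out by patients and informal caregivers, their frequency and the timing of completion are detailed in Table 3". It then describes the bereavement contact in one sentence: "If the patient dies the informal caregiver is asked to fill out the questionnaire once more 12 weeks after the death".

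The last column of Table 3 is headed "12 weeks after patient’s death". Among the caregiver rows, "General Health SF-36" and PHQ-9/HADS are marked in that column. The FAMCARE row reads "FAMCARE X X X X X" and stops one column short. The caregiver illness-understanding row stops at the same place.

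**The concern.** An objective needs an instrument and a time point at which it is given. Post-death satisfaction has the instrument, and a post-death assessment exists, but the schedule does not bring the two together. An analysis plan cannot repair this later, because it cannot analyse a form that was never handed out.

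The bereaved caregiver is the person able to look back on the whole course of care, including its last weeks. For patients who die before the first follow-up at week 12, the post-death contact is also the only scheduled point after randomization at which the caregiver could rate care at all. If FAMCARE is left out there, these caregivers contribute nothing to the comparison of satisfaction between arms.

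**Working it through.** No sample-size figure enters this point; that calculation concerns the patients' EORTC QLQ-C30 only. The check sets the objective against the schedule and adds one small piece of arithmetic.

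**Step 1. Marks in the caregiver part of Table 3.** The six columns are baseline, weeks 12, 18 and 24, the continuation column, and 12 weeks after death.

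| Caregiver form | Outcome | Marks | Marked after death? |
|---|---|---|---|
| SF-36 | quality of life | 6 | yes |
| PHQ-9 and HADS | mood | 6 | yes |
| FAMCARE | satisfaction | 5 | no |
| Illness-understanding questionnaire | illness understanding | 5 | no |

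The two rows above FAMCARE carry the sixth mark, and the FAMCARE row keeps its empty last cell. The blank therefore does not look like a fault of text extraction.

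**Step 2. Objective against schedule.** The time phrase in the objective can be read in two ways.

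- It applies to satisfaction only. Two outcome-period combinations are then at issue, satisfaction during treatment and after death, and the second has no form.
- It closes the whole list. Four outcomes over two periods make eight combinations. Table 3 covers all four during treatment and two after death (quality of life and mood), so 6 of 8. Satisfaction and illness understanding after death are missing.

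Post-death satisfaction is uncovered on both readings. Post-death illness understanding is uncovered on the second only.

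**Step 3. Text against schedule.** The sentence on the post-death contact speaks of one questionnaire and names no form. It neither includes nor excludes FAMCARE. Table 3 separates the forms row by row, and the same paragraph defers to it.

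**Step 4. Deaths before the first follow-up.** The article expects approximately 80 % of patients to be alive at 12 weeks, so about 100 % − 80 % = 20 % will have died. Of 182 patients, 0.20 × 182 = 36.4, or about 36. Under Table 3, and assuming the regular six-weekly forms stop at death, caregivers of these patients have FAMCARE at baseline only. Baseline is completed before randomization, so that score cannot reflect the intervention. Naming a caregiver is optional and no caregiver number is given, so about 36 is an upper limit under the article's own survival figure, not an estimate.

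**Step 5. Deaths after week 12.** FAMCARE is scheduled every six weeks from week 12. On the same assumption, the last scheduled rating falls within about six weeks before death, if it is completed.

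**The case against.** The best counter-argument is the text itself. At baseline the caregiver questionnaire includes FAMCARE, so the instruction that "the informal caregiver is asked to fill out the questionnaire once more 12 weeks after the death" can be read as the full set of forms, in line with the objective. Table 3 would then merely lack a mark. This stands to the extent that it prevents treating the omission as a settled decision. It does not remove the problem: the section refers to Table 3 for timing, and on this reading Table 3 is wrong.

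It is also fair to say that most of objective 2 is served. All four outcomes are collected during treatment, and quality of life and mood are collected after death. For deaths after week 12, only the last weeks and the retrospective view are lost.

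Three stronger inferences are tempting and are not supported:

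- A reader might infer that pre-death FAMCARE scores will be carried forward and reported as post-death results, because the article applies last observation carried forward to all missing data. A form that was never scheduled is not ordinarily a missing observation, and nothing in the article says such a value would be created.
- A reader might infer that all post-death satisfaction data are absent by deliberate design. The article shows an inconsistency, not a decision.
- A reader might infer that most caregivers of the 182 patients would be due the post-death form. The one-year life expectancy is an oncologist's approximate judgement for eligibility, follow-up length is not stated, and caregivers are optional.

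**Conclusion.** The point holds as an internal contradiction. The objective claims post-death satisfaction, the table does not schedule its only instrument, and the text leaves the content of the post-death form open. If Table 3 is applied as printed, that part of the objective cannot be answered. Caregivers of patients who die before week 12, at most about 36 if every patient names one, would have no satisfaction score from after randomization. That number rests on the article's expected 80 % survival at week 12 and on regular forms ending at death.

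It would go too far to say that objective 2 as a whole fails. One outcome-period combination is affected for certain, and a second (illness understanding after death) if the time phrase covers the whole list. The primary outcome, the sample size, satisfaction during treatment, and quality of life and mood after death are untouched. The correction should still be made, because bereavement ratings not collected at the time are hard to recover.

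**What to change.** Choose one of two routes and make the objective, the text and Table 3 agree.

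1. Mark FAMCARE in the post-death column of Table 3, name the forms in the sentence on the post-death contact, and compare the arms on that score. Word the objective so that illness understanding is claimed for the treatment period only. The form is already translated and tested and the assessment is already planned, so the cost is a few extra minutes for bereaved caregivers.
2. If FAMCARE is not to be given after death, reword objective 2 so that only quality of life and mood are claimed for that period, and state in the text that only SF-36 and PHQ-9/HADS are completed then. This changes wording only, but gives up the bereaved caregivers' view of care.

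The first route is preferable because it keeps the objective at little cost.

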#### Measurement instruments

The socio-demographic and clinical characteristics of the patient will be collected at baseline by using questionnaires for the patient and the physician and by consulting the medical record.

##### Patient and informal caregiver questionnaires

Quality of life of the patient will be measured with the use of the European Organisation for Research and Treatment of Cancer Quality of Life Questionnaire (EORTC QLQ C30) and the McGill Quality of Life Questionnaire (MQOL) [17–19]. The MQOL has been selected because it addresses the existential aspects of quality of life as well as the physical, emotional and social aspects of quality of life. A recent review qualified both its content and construct validity as high [20]. The mood of the patient will be measured by two instruments: the Hospital Anxiety and Depression Scale (HADS) and the Patient Health Questionnaire 9 (PHQ-9) [21–24]. Illness-understanding will be measured by a forward-backward translation of the questionnaire developed by the researchers of the previously mentioned study of palliative care for patients with metastatic non-small-cell lung cancer [4]. Data on mood, quality of life, illness understanding and satisfaction with care of the informal caregivers will be obtained by self-assessment instruments: HADS, PHQ-9, the Short Form-36 Health Survey (SF-36) a questionnaire for illness understanding and by the FAMCARE respectively [25]. A forward-backward translated and tested version of the FAMCARE will evaluate the satisfaction with care of the informal caregivers [26].

The surveys filled out by patients and informal caregivers, their frequency and the timing of completion are detailed in Table 3. The patient will complete the baseline questionnaires before randomization and the follow-up questionnaires with regard to quality of life, mood and illness-understanding firstly after 12 weeks and thereafter every six weeks. Change from baseline to 12 weeks after inclusion is chosen because approximately 80 % of patients are expected to be alive at 12 weeks after inclusion [4]. The informal caregivers will complete the baseline questionnaire before randomization and the follow-up questionnaires firstly after 12 weeks and then every six weeks. If the patient dies the informal caregiver is asked to fill out the questionnaire once more 12 weeks after the death.

**Table 3 Tab3:** Types of patient and informal caregiver questionnaires and frequency and timing of completion

	Week					
	Baseline	12	18	24	…	12 weeks after patient’s death
PATIENT FORMS						
EORTC QLQ C30 and MQOL	X	X	X	X	X	
PHQ-9 and HADS	X	X	X	X	X	
Illness-understanding Questionnaire	X	X	X	X	X	
INFORMAL CAREGIVERS FORMS						
General Health SF-36	X	X	X	X	X	X
PHQ-9 and HADS	X	X	X	X	X	X
FAMCARE	X	X	X	X	X	
Illness-understanding Questionnaire	X	X	X	X	X	

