**Methods/Design:**

A randomized controlled trial will be conducted as follows: 182 patients with advanced cancer will be recruited from the departments of Medical Oncology, Digestive Oncology and Thoracic Oncology of the Ghent University Hospital. The trial will randomize patients to either systematic early integration of palliative care in standard oncology care or standard oncology care alone. Patients and informal caregivers will be asked to fill out questionnaires on QoL, mood, illness understanding and satisfaction with care at baseline, 12 weeks and every six weeks thereafter. Other outcome measures are end-of-life care decisions and overall survival time.

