## Methods

### Study design

This is a phase III randomized controlled trial (RCT) in a hospital setting with advanced cancer patients receiving systematic early integration of palliative care with standard oncology care versus advanced cancer patients receiving standard oncology care alone. Study participants will be randomized in a 1:1 fashion to the intervention arm or standard care arm. Patients will be recruited from the Digestive Oncology, Thoracic Oncology and Medical Oncology departments of the Ghent University Hospital, the second largest hospital in Belgium. These departments have been selected for the trial because almost all cancer patients in the Ghent University Hospital are treated in these departments. Stratification will take place for the treating oncology department (Digestive Oncology, Thoracic Oncology and Medical Oncology) in order to prevent imbalances between groups in factors related to possible differences in standard care [15].

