#### Statistical analysis and sample size calculation

To compare baseline characteristics and study outcomes for patients between groups, Fisher’s exact tests, chi-square tests and the independent-samples t-test or the non-parametric equivalent Mann–Whitney *U* will be used. The effect of early palliative care on the primary outcome quality of life will be assessed by multivariate regression analyses adjusting for baseline scores. Survival analysis, i.e. Kaplan-Meier and a Cox proportional hazards model, will be used to examine the effect of systematic early integration of palliative care on the secondary outcome survival from the time of inclusion adjusting for demographic and clinical baseline characteristics. With regard to missing data, we will use the conservative approach of carrying the last observation forward for all missing data.

To detect a significant and meaningful difference in the change of the EORTC QLQ-C30 from baseline to 12 weeks, 118 patients are needed. With the proposed sample size of 59 for the two groups, the study will have a power of 80 % to yield a statistically significant result. This computation assumes a mean score difference of 12 and the common within-group standard deviation is 23.0. A difference of 10 points on the multi-items scales from 0 to 100 is considered meaningful (50;51). On the basis of the study on early palliative care in advanced lung cancer patients, it can be expected that approximately 80 % of the study participants will still be alive at 12 weeks after inclusion and drop-out for reasons other than death will amount to 15 % [4]. In other words, an overall drop-out rate of 35 % is to be expected, accounting for the planned inclusion of a total of 182 patients in the study.

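### No patient-reported outcome is scheduled between baseline and week 12, so for the roughly one-third of patients expected to be unavailable by then, the planned carry-forward uses the pre-randomisation value

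*Protocol article*

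**What the plan says.** The section on patient and informal caregiver questionnaires has the follow-up forms completed "firstly after 12 weeks and thereafter every six weeks". The abstract gives the same schedule, "at baseline, 12 weeks and every six weeks thereafter", and the columns of Table 3 run baseline, 12, 18, 24 and onward. This covers the QLQ-C30, MQOL, HADS, PHQ-9 and illness-understanding questionnaire. The reason given for week 12 is that about 80% of patients should still be alive then.

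The section on statistical analysis and sample size makes the change to week 12 the basis of the design: "To detect a significant and meaningful difference in the change of the EORTC QLQ-C30 from baseline to 12 weeks, 118 patients are needed". It expects about 80% alive at that point, adds that "drop-out for reasons other than death will amount to" 15%, sums the two losses to 35%, and raises the total to 182. The same section carries the last observation forward wherever data are missing.

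**The concern.** The six-weekly interval used for the rest of follow-up is not used in the first 12 weeks. A patient who dies or leaves in that time has no patient-reported value after randomisation, so the last observation is the baseline. Carrying it forward enters a change of exactly zero for someone who may have deteriorated and died.

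Two things are at stake. First, the primary comparison is diluted when loss is equal in the two arms. When loss differs by arm it can be biased in either direction, and the trial is unblinded with survival as a secondary outcome, so equal loss cannot be taken for granted. Second, patient-reported decline before loss cannot be examined, because nothing was scheduled that could show it. Early mood change is likewise unmeasured, although intervention patients meet the palliative care nurses at least monthly from the start and the Discussion reports clinicians' concern that referral may alarm patients.

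**Working it through.** **Inputs from the article.** Difference 12 and SD 23.0 ("This computation assumes a mean score difference of 12 and the common within-group standard deviation is 23.0"); 59 per arm with power of 80% ("With the proposed sample size of 59 for the two groups, the study will have a power of 80"); 1:1 allocation; 20% dead at week 12; 15% other drop-out; 182 randomised. The significance level is not stated. Two-sided 0.05 is assumed because it reproduces the stated size (one-sided 0.05 would give 46 per arm).

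**Step 1: reproduce the plan's figures.**
- n per arm = 2 × (1.96 + 0.842)² × 23² / 12² = 57.7, so 58. The t-test version gives 58.6, so 59 per arm and 118 in total. Power at 59 per arm is 0.802 (t-test).
- 118 / (1 − 0.35) = 181.5, so 182.

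Both stated figures are right. The inflation works only if the whole 35% is unavailable at week 12, so the plan's own arithmetic places the loss before that endpoint.

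**Step 2: patients without a week-12 value.**
- Additive, as planned: 0.35 × 182 = 63.7, about 64 (36.4 deaths plus 27.3 other drop-outs).
- If the 15% applies only to survivors: 1 − 0.80 × 0.85 = 0.32, and 0.32 × 182 = 58.2, about 58.

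**Step 3: effect of carrying baseline forward.** Assume equal loss in both arms and a true difference of 12 among patients with a week-12 value.
- Expected difference over all 182: 0.65 × 12 + 0.35 × 0 = 7.8 points (0.68 × 12 = 8.2 with 32% loss).
- Power with 91 per arm and SD still 23: 7.8 / (23 × √(2/91)) = 2.29, giving about 63%.
- The imputed zeros also shrink the SD. With SD 23 × √0.65 = 18.5 in both arms, power is about 81%. If the intervention arm's SD is instead √(0.65 × 23² + 0.35 × 0.65 × 12²) = 19.4, power is about 79%.

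The estimate is therefore clearly diluted. Whether power falls depends on what happens to the SD.

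**Step 4: what a week-6 form would add.** The article does not give the timing of losses, so it is assumed here.

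| Assumed timing of loss | Lost by week 6 (still no post-baseline value) | Gain a scheduled week-6 value |
|---|---|---|
| Constant rate: 1 − √0.65 = 0.194; × 182 | 35.3 | 63.7 − 35.3 = 28.4 |
| One-third before week 6 | 21.2 | 42.5 |
| Two-thirds before week 6 | 42.5 | 21.2 |

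The last column gives maxima, since some week-6 forms will also be missed.

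**The case against.** The strongest reply is that this is an open and sized design choice. Week 12 has a stated rationale, the schedule is consistent throughout the article, and 182 is set so that about 118 patients are observed at the endpoint. That stands as far as it goes: a reader might infer that the sample size is wrong, and it is not. But sizing for loss protects power among observed patients; it does not remove the bias from how the others are entered. The survival rationale also supports week 12 as the primary time point without explaining why nothing is measured before it.

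Other readings go further than the article allows:
- **That no patient outcome at all is collected before week 12.** Survival runs from inclusion, and chemotherapy intensity, admissions and professional contacts come from medical records. Only patient-reported outcomes wait.
- **That the comparison rests on healthier survivors.** The carry-forward rule, read literally, keeps lost patients in the analysis with a change of zero. The fault is that imputed zero, not their exclusion.
- **That the first 12 weeks are the period of heaviest loss.** The plan states losses for no other period.
- **That exactly 64 patients will have nothing after baseline.** Only the 20% mortality is expressly dated to week 12. The timing of the 15% is inferred from the endpoint, and someone who merely misses week 12 could return at week 18. The figure is an upper one.
- **That dependence of loss on decline cannot be studied at all.** Loss by arm, baseline predictors, time to death and record-based events remain available. Only patient-reported decline is out of reach.

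It is also fair that a week-6 form alone does little for the primary endpoint: under the present rule, week 6 would simply be carried forward instead. The schedule and the missing-data rule have to change together. The Edmonton symptom scores do not fill the gap, because they belong to the intervention consultations and are not listed as an outcome.

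**Conclusion.** The point holds for patient-reported outcomes. Up to about 64 of 182 patients (about 58 if the losses compound) are expected to have only a pre-randomisation value at the primary time point, and the plan's rule turns that into a change of zero, deaths included. The assumed 12-point difference becomes about 7.8, which rests on equal loss in both arms and on carry-forward being applied to everyone randomised. The size calculation is sound. An earlier assessment is worth having but only a partial cure: about 28 patients gain a value at a constant loss rate, 21 to 42 over the assumed range of timings, and about 35 (21 to 42) would still have none.

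**What to change.** Add a week-6 column to Table 3 for a reduced patient set, at minimum QLQ-C30, HADS and PHQ-9, with a collection window. Keep week 12 as the primary time point.

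Replace the carry-forward rule for the primary outcome with wording such as: *QLQ-C30 scores at weeks 6 and 12 will be analysed in a likelihood-based repeated-measures model with baseline score, arm, visit, arm-by-visit interaction and oncology department; the primary estimate is the arm difference at week 12. Patients alive but missing at week 12 contribute through their week-6 value. Baseline values will not be carried forward. Deaths before week 12 will not be imputed as unchanged; how they enter the comparison will be stated, and deaths will be reported by arm beside the estimate.*

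The cost is a schedule amendment and one short questionnaire round, for about 182 − 35 = 147 patients at a constant loss rate. That adds patient burden, which matters because the ethics section foresees distress from completing the forms. It also adds collection effort, which cannot be assumed free because the article does not say how follow-up forms are staffed. The new form helps only patients who have not passed week 6 when it takes effect; the analysis change applies to all.
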